#### Statistical analysis

The purpose of this study is to confirm whether the therapeutic effect of experimental therapy (fire needle cupping) is different from that of reference therapy (famciclovir plus gabapentin and fire needle cupping plus famciclovir). SPSS 20.0 statistical software will be used for data analysis. When the main efficacy indicators of individual subjects are missing, the last observation carried forward will be conducted, and the non-main efficacy indicators will not be carried forward. The mean ± standard deviation is used for statistical description of measurement data, and the frequency (constituent ratio) is used for statistical description of counting data. The baseline characteristics will be recorded as in Table 3. The group *t* test (Bonferroni method) will be used to compare the measurement data between groups. All reported *P* values will be two-tailed with 95% confidence intervals. The value of *P* ≤ 0.05 will be considered statistically significant. PPS analysis and Fas analysis will be performed at the same time. SS analysis is used for safety evaluation.

**Table 3 Tab3:** Baseline characteristics

Characteristics	Value
Age, mean ± SD, year	
Gender, *n* (%)	
Male	
Female	
Onset days, mean ± SD, days	
VAS score, mean ± SD	
Quantitative score, mean ± SD	

Onset days are the time from the patient’s onset of pain or rash to inclusion

Quantitative score is quantitative score of symptoms and signs

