**Fig. 1 Fig1:**
[figure not shown]
The flow chart of the trial

The visual analogue scale (VAS) scores, symptoms, and physical scores are obtained for pre- and post-treatment periods. The concentrations of SP and β-Ep in peripheral plasma will also be detected, and demand for temporary analgesics and side effects of the patients are recorded daily. As the final stage, after 6 months, the participants are to be followed up for postherpetic neuralgia, 6 months after treatment (Fig. 2).

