### Participants

#### Inclusion criteria

Eighteen to 60 years old, with no gender difference.Skin rash and clustered blister in asymmetrical skin area.Precursor symptoms such as general discomfort and fatigue before rash.Nervous pain in the affected area, skin hypersensitivity.The rash is distributed along the innervated area.Unilateral, not exceeding the midline of the body.Pain intensity as assessed by VAS (0–100 mm) of 50 mm δ pain intensity δ80 mm.

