#### Management of dropout cases

For dropout cases, researchers should actively take measures to complete the last laboratory test as far as possible in order to analyze its efficacy and safety. For all dropout cases, the test conclusion form and reason for dropout shall be filled in the case report form.

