### Intervention

#### Group A

This group will be treated with only FC.
Acupoints: the main points are Ashi points (lesion area), corresponding nerve segment Jiaji points, and branch ditch points (SJ6); matching points are selected according to syndrome differentiation, pattern of dampness-heat in the liver meridian with Yang Ling Quan (GB34), pattern of dampness-heat in the spleen meridian with Yin Ling Quan (SP9), and pattern of obstruction of collaterals by blood stasis with blood sea (SP10).Appliances: medium-sized fire needle (diameter 0.4 mm), large-sized fire needle (diameter 0.65 mm), glass fire cup no. 1–5, medical cotton ball, alcohol lamp, lighter, iodophor, etc.Operational methods: routine disinfection of the skin with iodophor with the order of the head, middle, and tail of herpes will be carried out firstly. Holding 95% alcohol lamp by the left hand close to the needle, and to burn the needle in the right hand to whitening by the external flame of the fire, acupuncturist will prick the head of the herpes cluster. Then, the needles will be pricked into the blisters or rashes quickly from the surface of the skin to the base of the herpes. Pricking early-onset herpes at first, for larger pustules or blood blisters (diameter ε0.5 cm) with a large-scale fire, acupuncturist will extrude blister fluid with disinfection cotton ball after puncture, and then cup with a suitable size of glass fire cup for 5–10 min. If the area of the herpes cluster is too large, more than one cup can be used. The remaining acupuncture points are treated with fire needle pricking, and each acupuncture point should be pricked three times. Finally, the skin should be sterilized with iodophor more than one time. The treatment should be performed once a day for a total of 7 days.Skin care: after treatment, the iodophor is used to clean and disinfect the skin and to keep the patient’s skin dry and clean during the treatment.Course of treatment: the course of treatment is 1 week and from one to seven times. If there is no pain any more after one time of FC treatment, the course is just one time. Meanwhile, if the patient is still suffering pain, the FC will continue once a day unless the pain disappears. All the treatments will not be more than seven times no matter the pain or not.

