### Outcomes

#### Primary outcome

The primary outcome has been the changes in pain intensity pre- and post-treatment (VAS 0–100 mm, where 0 = *painless* and 100 = *maximum imaginable pain*).

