This study is intended to design a rigorous trial protocol that will yield evidence on effective acupuncture technique. In that, this study should be closer enough to the clinical real-world research. Nevertheless, there are confounding factors associated with this designed trial that cannot be completely avoided. First, there is no separate set of sham acupuncture as a control group for FC treatment. Since the first group of FC treatment is already a combination of two types of acupuncture techniques, it is hard to implement another set of sham acupuncture. Another issue of the ethical principle will also make it difficult to perform sham acupuncture for FC treatment since conflicts of interests may happen for patients who have already suffered from severe pain and will not be likely to accept sham acupuncture. Note that, however, the psychological effects cannot be ruled out for lack of sham acupuncture group [17–19]. Second, the blind method is also impossible to perform under the current designed trial since it is not possible for acupuncturists and subjects to do so under the operation of FC treatment. Instead of blinding, the FG and FCF treatments have both been designed to set as the control interventions. As such, the results from FG would be good enough to give evidence of comparison and FCF is also a good way to show whether the combination of drug with FC treatment will yield a better result than the FC treatment alone. Third, as in our clinical practice, acute pain associated with AHZ infection tends to be amplified alongside with the development of the AHZ disease. Therefore, as an intra-trial arrangement, the temporary short-acting painkillers will be permitted to all the selected patients regardless of their group divisions. Having such intra-trial, temporary, and low dose pain release drugs will have no obvious effect on the results. Another limitation of this trial is the psychological factors that cannot be eliminated according to the present design, and the difference in immunity is relative to the recovery of HZ which may lead to differences in prognosis. Finally, according to the actual clinical situation, the drug dose, as well as the number of FC treatment interventions, has certain volatility and does not restrict sternly.

In all, this protocol will act to provide a reference of clinical methodology and may give definite evidence on the effect of FC intervention for AHZ as it is designed.

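### On the VAS times given in the text, last observation carried forward scores a patient with no VAS after baseline as exactly zero pain relief and treats that as observed

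*Protocol article*

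**What the plan says.** Under Primary outcome: "The primary outcome has been the changes in pain intensity pre- and post-treatment", on a 0 to 100 mm VAS. The Study design text gives the timing: "The visual analogue scale (VAS) scores, symptoms, and physical scores are obtained for pre- and post-treatment periods". What it lists as collected every day is something else: "demand for temporary analgesics and side effects of the patients are recorded daily".

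Under Statistical analysis, the rule for missing primary data is "When the main efficacy indicators of individual subjects are missing, the last observation carried forward will be conducted". Other indicators are not carried forward. Groups are compared by t test with a Bonferroni method, in both a full analysis set and a per-protocol set. No other handling of missing primary data is stated.

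Three further places bear on the point:
- Management of dropout cases says that "researchers should actively take measures to complete the last laboratory test as far as possible". VAS is not named.
- Under Group A, the fire needle and cupping (FC) course may end after a single session; otherwise "the FC will continue once a day unless the pain disappears", up to seven sessions. Group C follows the same course.
- The Discussion says that "acute pain associated with AHZ infection tends to be amplified alongside with the development of the AHZ disease".

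**The concern.** Carrying the last value forward assumes that a patient's pain would have stayed where it was last seen. The protocol describes the opposite: pain that may be gone after one session, or that builds as the disease develops.

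With one value before and one after treatment, the only earlier value is the baseline, which the inclusion criteria place at 50 to 80 mm. A patient in group A or C who becomes pain-free, stops treatment early and does not return would be recorded as having had no relief. That zero then enters the t test as if it had been measured.

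The text also does not tie the post-treatment VAS to day 7. Where an FC course ends early, the assessment could fall on a different day from group B's, which adds to the uncertainty about what is being carried forward and to when.

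Treatment is open, and the burdens differ by arm: daily sessions with a risk of burns in A and C, tablets alone in B. Unequal missingness is therefore plausible, although the documents give no figure for it. Any inequality would pass directly into the estimated treatment difference.

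**Working it through.** **The plan's own figures.** With λ = 12.654 (2 degrees of freedom, alpha 0.05, power 0.90) and an arcsine difference of 0.890 between 0.80 and 0.378, n = 2 × 12.654 / 0.890² = 31.95. That gives 32 per group and 96 in all, and 96 × 1.09 = 104.6 gives 105. The sample size reproduces. It matters here only because it shows that about 9 to 10% dropout is expected, with 35 patients per arm.

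**Inputs not in the documents (assumptions).** Mean fall in VAS of 40 mm (range 30 to 50); SD of change 20 mm; missing patients have the same true mean change as completers and have only a baseline value; three pairwise comparisons, so the Bonferroni level is 0.05/3 = 0.0167.

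**Step 1: imputed value.** Change = baseline − baseline = 0 mm. With missing fraction d and true mean change m, the expected estimate in an arm is (1 − d) × m.

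**Step 2: equal missingness, d = 0.10 in both arms.**
- True difference 10 mm (40 v 30): 0.9 × 40 − 0.9 × 30 = 9 mm, a loss of 10%.
- SD of change: √[(1 − d)s² + d(1 − d)m²] = √[0.9 × 400 + 0.09 × 1600] = √504 = 22.4 mm, against 20 mm.
- No true difference: expected difference 0, and type I error stays nominal (step 4).

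**Step 3: unequal missingness, no true difference.** False difference = m × (d₂ − d₁). For 10 percentage points:

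| Assumed mean fall | False difference |
|---|---|
| 30 mm | 3 mm |
| 40 mm | 4 mm |
| 50 mm | 5 mm |

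The sign favours the arm with less missing VAS.

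**Step 4: type I error.** Simulated two-arm t tests with 35 per arm, a 40 mm mean fall in both arms, SD 20 mm, and missing patients set to 0:

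| Missing VAS, two arms | Expected patients (of 35) | At 0.05 | At 0.0167 |
|---|---|---|---|
| 10% v 10% | 3.5 v 3.5 | 5% | 1.6% |
| 8% v 12% | 2.8 v 4.2 | about 6% | about 2% |
| 5% v 15% | 1.75 v 5.25 | about 11 to 12% | about 5% |

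All three rows average 10% missing, close to the planned dropout.

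**Step 5: if a later, unscheduled VAS exists.** The rescue ladder under Temporary analgesics uses VAS bands that begin at 50 mm. A value recorded to trigger rescue is therefore at least as high as the lowest admissible baseline. It was taken because pain was bad at that moment. Carrying it forward replaces one unsuitable value with another.

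**The case against.** The strongest reply is that the decisive schedule cannot be seen. Figures 2 and 3 hold the time schedule and are not shown, and they might list more VAS times. That stands as a limit: the point holds on the times given in the text and no further.

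Second, VAS bands govern rescue in all three arms, so some patients will have later values. This also stands, and the exact zero therefore applies only to patients with no VAS after baseline. The FC stopping rule speaks only of pain disappearing, so it cannot be cited as already requiring a daily VAS.

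Third, a reader might infer that every dropout is scored as no relief. The documents do not support that. Their dropout list includes poor compliance, protocol violation and loss at the final stage, and none of these by itself means that the post-treatment VAS is absent. For the same reason, the arm-specific compliance rules do not show unequal missing VAS. The last test sought from dropouts is also meant to serve efficacy, which may reduce missingness, although VAS is not named.

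Fourth, a reader might infer a severe false-positive problem, near 20% at 0.05. That needs something like 5% v 20% missing. Such a split averages 12.5%, above the planned 9 to 10%; no passage supports an imbalance of that size; and the 0.05 level ignores the Bonferroni step. With mild imbalance at the planned dropout, the inflation is small. Nor do the documents show which arm would gain.

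Finally, a per-protocol analysis runs alongside, and the choice of model is often left to an analysis plan. But the per-protocol set selects on adherence, so it is no unbiased check. The article does not leave the method open: it names one. A later plan could not recover VAS values that were never collected.

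**Conclusion.** The point holds in a limited form and should be fixed. On the VAS times in the text, the stated rule gives patients with no VAS after baseline a change of exactly 0 mm, or else carries forward a rescue-time peak. Both conflict with the changing pain that the protocol itself describes.

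Balanced missingness costs precision and dilutes the effect but leaves type I error near nominal. Unbalanced missingness produces a false difference of a few millimetres in an unknown direction, with type I error ranging from barely raised to roughly double or triple nominal across the imbalances examined at about 10% overall missing. These sizes rest on the assumed falls, SD and missing fractions listed above. The mechanism rests only on the assessment times in the text.

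**What to change.** - Define the primary time point as the VAS on day 7 for every randomised patient, whether or not treatment ended early or was stopped.
- Under Management of dropout cases, add VAS to what is sought from dropouts.
- Add a VAS line to the daily record, next to the day 1 to 7 analgesic entries in Table 2.
- In the primary analysis, replace last observation carried forward with a baseline-adjusted mixed model for repeated measures, with the day-7 contrast as primary, or with multiple imputation that uses the daily VAS.
- Keep last observation carried forward only as a sensitivity analysis.
- If Figures 2 and 3 already list further VAS times, say so in the text and state which values count.

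The cost is one more line on a form already completed daily, a day-7 contact for patients who finish or stop early, and slightly more analysis work. No treatment or stopping rule changes.

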### Randomization and allocation concealment

Block setting: 105 participants are numbered 1–105 according to the time of participation, the block length is 6, and 16 blocks are set.Obtaining random numbers: start with any two-digit number in the random number table, and take 105 numbers to the right.Grouping: 6 random numbers of each block are sorted from small to large, sorts 1 and 2 are group A, sorts 3 and 4 are group B, and sorts 5 and 6 are group C.Random group concealment: the grouping conditions of participants are packed into 105 envelopes, and all the envelopes are numbered in order and sealed. To ensure the randomization process, the serial number will be printed on the outside of the opaque envelope and the assignment of the group will be sealed on the inside of the envelope.

[name], an otolaryngologist at the Sixth Affiliated Hospital of Kunming Medical University, is responsible for the above matters, and she does not get involved in the process of treatment and the data collection of this study.

The envelope will be opened according to the patient’s serial number, and the dermatologists will be responsible to inform patients by phone on their random number and assignment.

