### Statistical methods

#### Sample size estimation

We will compare the difference in efficacy of the three groups. Sample size estimation is based on the method of the book of *Health statistics* [15], with type I error alpha = 0.05 and type II error beta = 0.1, using the bilateral test. According to the literature, the cure rates of famciclovir and for fire needle plus cupping for HZ were 37.8% and 76.4%, respectively. It was speculated that the cure rate of famciclovir plus fire needle plus cupping was 80.0%, which was substituted into the formula:

$$ n=\frac{2\lambda }{{\left(2{\sin}^{-1}\sqrt{p_{\mathrm{max}}}-2{\sin}^{-1}\sqrt{p_{\mathrm{min}}}\right)}^2} $$where *P*_max_ = 0.80 and *P*_min_ = 0.378. The calculated result was a sample size of 32 subjects per group. Therefore, the number of samples required for the three groups was 96. This study required a total of 105 samples adding a 9–10% dropout rate.

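### The primary VAS comparison is an unadjusted t test on change: valid, but a prespecified ANCOVA on recorded baseline VAS and onset days would be at least as precise at almost no cost

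*Protocol article*

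**What the plan says.** Under Primary outcome the protocol article states: "The primary outcome has been the changes in pain intensity pre- and post-treatment", on a 0–100 mm VAS. Under Statistical analysis, continuous data are compared by a group t test ("Bonferroni method) will be used to compare the measurement data between groups"). That sentence covers measurement data in general. No other test is offered for VAS change, so the two sections together fix the primary comparison. No covariate or regression model is named.

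On baseline data the same section says: "The baseline characteristics will be recorded as in Table 3". Table 3 includes "VAS score, mean ± SD" and "Onset days, mean ± SD, days", with the footnote "Onset days are the time from the patient’s onset of pain or rash to inclusion". Randomization and allocation concealment describes blocks of six and mentions no stratification by baseline pain or time since onset.

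Sample size estimation arrives at 32 per group: "This study required a total of 105 samples adding a 9–10% dropout rate". Three equal groups make 35 randomised per arm.

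**The concern.** A change score uses baseline VAS, but only by subtracting it, which fixes the slope of post-treatment on baseline VAS at 1. The true slope is unknown. If it differs from 1, the change score carries avoidable variance, and a chance difference in baseline means is over- or under-corrected. ANCOVA estimates the slope from the data.

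Onset days receive no adjustment at all. The inclusion criteria set no limit on time since onset, and the Discussion says that acute pain tends to grow as the disease develops. Patients who enter at different stages may therefore have different expected one-week changes.

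At stake are the width of the confidence intervals for the primary contrasts, and how the result can be read if Table 3 shows an imbalance. If no adjusted analysis is fixed in advance, a later choice between adjusted and unadjusted results could depend on the data.

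**Working it through.** **The plan's own figure.** The stated formula is n = 2λ / (2·asin√0.80 − 2·asin√0.378)². Take λ = 12.654, the noncentrality of a 2-df chi-square at alpha 0.05 and power 0.90. The bracket is 0.890 and its square 0.792, so n = 25.308 / 0.792 = 31.95, or 32 per group and 96 in total. Then 96 × 1.09 = 104.6, or 105. The figure reproduces. It rests on cure rates, so it supplies neither an SD nor a correlation for VAS.

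**Inputs for the comparison.**
- Entry range of VAS, 50 to 80 mm: Inclusion criteria.
- Baseline SD s_b = 30/√12 = 8.66 mm: assumption, uniform over the entry range.
- Post-treatment SD s_p = 15, 20 or 25 mm, and pre–post correlation r = 0 to 0.7: assumptions, since the article gives neither.

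**Formulas (per-patient variance, large sample).**
- Change score: s_b² + s_p² − 2·r·s_b·s_p
- ANCOVA on baseline VAS: s_p²·(1 − r²)
- Gain in equivalent patients: (change variance / ANCOVA variance) − 1 = (s_b − r·s_p)² / [s_p²·(1 − r²)]
- Slope of post-treatment on baseline VAS: r·s_p / s_b

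The gain is a square over a positive quantity, so it is never negative. It is zero when the slope is 1.

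Example at r = 0.2, s_p = 15: the change variance is 75 + 225 − 52.0 = 248.0, the ANCOVA variance is 225 × 0.96 = 216.0, and the gain is 14.8%.

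| r | s_p = 15: gain (slope) | s_p = 20: gain (slope) | s_p = 25: gain (slope) |
|---|---|---|---|
| 0 | 33.3% (0) | 18.8% (0) | 12.0% (0) |
| 0.2 | 14.8% (0.35) | 5.7% (0.46) | 2.2% (0.58) |
| 0.3 | 8.5% (0.52) | 1.9% (0.69) | 0.2% (0.87) |
| 0.4 | 3.7% (0.69) | 0.1% (0.92) | 0.3% (1.15) |
| 0.5 | 0.8% (0.87) | 0.6% (1.15) | 3.1% (1.44) |
| 0.6 | 0.1% (1.04) | 4.4% (1.39) | 10.0% (1.73) |
| 0.7 | 3.0% (1.21) | 14.0% (1.62) | 24.5% (2.02) |

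**Chance imbalance in baseline VAS.** The SE of the difference between two arms is 8.66 × √(2/32) = 2.2 mm, or 8.66 × √(2/35) = 2.1 mm. A difference of 4 mm is about 1.85 SE with 32 per arm, which any one pair of arms reaches or exceeds about 6.5% of the time.

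Given an imbalance d, the change-score estimate shifts by (slope − 1) × d. At r = 0.3 and s_p = 20 the slope is 0.69, so d = 4 mm gives (0.69 − 1) × 4 = −1.2 mm. At r = 0.5 and s_p = 15 it gives (0.87 − 1) × 4 = −0.5 mm. At r = 0.7 and s_p = 20 it gives (1.62 − 1) × 4 = +2.5 mm.

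**Onset days.** The article gives no spread for onset days and no relation to VAS, so no figure follows.

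**The case against.** The strongest reply is that nothing here is an error. A t test on change between randomised arms is unbiased with correct type I error, the change score already uses baseline VAS, and an article may leave covariates to the analysis plan. The first two points stand. The third stands only in part: the article commits to a named method, and the point concerns that choice, not missing detail.

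Four stronger readings are tempting, and the article does not support them.
- *The estimate is biased.* It is off only conditionally on an imbalance that has occurred. Averaged over randomisations it is unbiased.
- *Baseline imbalance passes whole into the result.* It enters as (slope − 1) × d. A shift of the full d in the direction opposite to the imbalance needs a slope of 0. In the middle of the range the shift is a fraction of d.
- *The narrow entry range forces the slope below 1.* A small baseline SD with a larger post-treatment SD pushes the slope up. Both sides of 1 appear in the table, and the gain at high correlation comes from slopes above 1.
- *The precision loss is large.* The 12–33% figure needs baseline pain to predict nothing. At correlations of 0.4 to 0.5 the gain is 0–4%. Larger gains derived from equal pre and post SDs would require a post-treatment SD of only about 8.7 mm if entry is uniform over the range.

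It is also fair to say that the requirement for clustered blisters and the exclusion of earlier painkiller use may limit late entry somewhat, and that any gain from onset days is speculative in size.

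**Conclusion.** The point holds as an efficiency improvement, not as a fault in validity. The stated test gives up some precision and some conditional protection against imbalance. Under the assumed SDs, the gain from adjusting for baseline VAS lies between about zero and a third more patients. It is small at moderate correlations and larger at low or high ones. No value in that range can be singled out, because the article gives no SD or correlation.

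The case for acting does not need a large gain. In large samples ANCOVA on baseline VAS is never less precise than the change score, and both covariates are already collected. A change to the analysis section is worth making before any outcome data are seen. The sample size is not affected.

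**What to change.** In Statistical analysis, replace the t test for the primary outcome with a prespecified ANCOVA of post-treatment VAS with terms for arm, baseline VAS and onset days. Report Bonferroni-adjusted pairwise mean differences with confidence intervals. Keep the unadjusted t test on VAS change as a sensitivity analysis.

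State that the baseline VAS is the one recorded before allocation is revealed. The article says "The envelope will be opened according to the patient’s serial number" and that patients are then told their group, but it does not clearly place the baseline rating before that step. In an open trial, a self-rated score taken afterwards could be influenced by the assignment.

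The endpoint stays at post-treatment, as the article defines it. The cost is one or two degrees of freedom: with 32 per arm, a pairwise comparison goes from 62 to 60 with both covariates. The stated software can fit the model, and no further data or patients are needed.
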